#### Research goal 3: Decision analytic model

Finally a decision analytic model is built which provides a framework combining available evidence from different resources among which (accuracy) results from the study, literature and expert opinion. A decision analytic model can be defined as a set of mathematical relationships that form a structure reflecting the natural progression of a disease. By simulating patients or fractions of a population, these models enable the estimation of the likelihood of each consequence and its corresponding costs and effects [48]. It is applied to evaluate the short-term cost-effectiveness in terms of cost per correct diagnosis and long-term cost-utility in terms of cost per quality adjusted life year gained of diagnostic strategies under evaluation. Utility scores will be used to calculate Quality Adjusted Life Years (QALY). Patients who pass away during the year covered by the evaluation will be given a utility score of zero from the exact time of death. QALYs will be derived using the trapezium rule. A societal viewpoint will be adopted including the evaluation of all relevant costs and effects to calculate the societal benefits.

The cohort design facilitates the evaluation of many different diagnostic procedures by varying the place of a new diagnostic marker in the clinical pathway. Each procedure generates specific proportions of correct or incorrect diagnoses. Average costs and effects of correct and incorrect diagnoses are applied to calculate the total costs and effects of each procedure.

Sensitivity analysis will be performed taking into account both first order uncertainty regarding variation between patients in a homogeneous group and second order uncertainty regarding the true value of the parameters included in the model. This also enables the evaluation of an earlier diagnosis, different test sequences and the effect of possible new disease modifying drug treatments.

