#### Research goal 1: Diagnostic test accuracy

Diagnostic test accuracy is determined by relating index test results to the reference diagnosis (reference test). All diagnoses consist of a dichotomous outcome value on underlying pathology of the clinical syndrome and on (expected) progression of cognitive decline within two years. Separately for aetiology and progression of cognitive decline each index test result for each case is indicated as either true positive, true negative, false positive or false negative based on the reference diagnosis (reference test). This enables the calculation of accuracy estimates: sensitivity, specificity, positive predictive value, negative predictive value, likelihood ratio and (an increase of) the Area Under the Curve of a Receiver Operating Characteristic curve.

Finally, novel innovative diagnostic tests are developed during the course of this study by other cooperating researchers for which proof of principle does not yet exist. These tests will be evaluated as soon as evaluation in clinical subjects is possible. To assess diagnostic accuracy the tests will be applied in subgroups of the cohort retrospectively (for CSF samples) or using a case–control design.

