#### Research goal 2: Cost-consequence and cost-effectiveness analysis

A cost-consequence analysis is performed listing all relevant costs and effects without aggregating it into a ratio [47] allowing decision-makers to choose the outcome of particular interest to include in an economic analysis. Average costs and consequences of the whole cohort are compared with the subgroup of patients who have received a correct diagnosis according to the reference test. This enables the comparison of the current diagnostic practice costs and effects and the costs and effects of an ideal situation (a costless diagnostic test with 100% accuracy). The difference indicates the maximum possible achievable benefit of new biomarkers for AD and related disorders in terms of costs and health effects. Furthermore, a cost-effectiveness analysis is performed comparing current practice with diagnostic procedures that include emerging biomarkers. The change in costs is compared to the change in diagnostic accuracy to obtain a cost-effectiveness ratio in terms of costs per correctly diagnosed patient.

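### As written, the decision model separates only correct from incorrect diagnoses, so downstream costs and QALYs depend on overall accuracy alone and not on sensitivity and specificity

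*Protocol article*

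**What the plan says.** The calculation rule stands in two consecutive sentences of the protocol article, section Research goal 3: Decision analytic model. The first says "Each procedure generates specific proportions of correct or incorrect diagnoses". The second says "Average costs and effects of correct and incorrect diagnoses are applied to calculate the total costs and effects of each procedure". Both the proportions and the values attached to them have two classes.

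The section Research goal 1: Diagnostic test accuracy goes further. There, separately for aetiology and for progression, "each index test result for each case is indicated as either true positive, true negative, false positive or false negative". These four cells feed the accuracy estimates. The goal 3 section does not mention them.

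The section on Research goal 2 pools in the same way: "Average costs and consequences of the whole cohort are compared with the subgroup of patients who have received a correct diagnosis", again without a split by disease status.

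The model is meant to deliver "long-term cost-utility in terms of cost per quality adjusted life year gained of diagnostic strategies under evaluation", and its sensitivity analysis is to cover, among other things, "the effect of possible new disease modifying drug treatments".

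**The concern.** A missed Alzheimer's disease (AD) patient and a patient wrongly labelled as having AD are both incorrect diagnoses, but nothing suggests that their costs or utilities are alike. The same goes for a true positive and a true negative, who differ in the disease itself. Pooling within each class has two consequences.

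- **No discrimination.** If two procedures have the same proportion correct, the rule must give them the same downstream costs and QALYs, however their errors divide.
- **No transfer.** The average for correct diagnoses blends true positives and true negatives in the ratio produced by whichever procedure supplied the data. The average for incorrect diagnoses blends false negatives and false positives in the same way. If the cohort under current practice supplies them, they reflect that operating point and do not carry over to a procedure with another one.

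Comparing many procedures is the model's purpose, so the incremental cost, the QALY difference and the ranking are all exposed.

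**Working it through.** The article states no figure for this rule, so there is nothing to reproduce. The check is algebra plus an illustration.

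**Inputs from the article.** Accuracy of current practice is 80% (section Sample size and missing data). The cohort has 241 patients (section Subjects).

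**Assumed inputs, because the article gives none.** Cost per patient in kEUR: TP 30, FN 36, TN 12, FP 15. Prevalence p = 0.5, then 0.3 and 0.7. Sensitivity and specificity as shown below. Tests' own costs are left out.

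**Formulas.** TP = p·Se, FN = p·(1−Se), TN = (1−p)·Sp, FP = (1−p)·(1−Sp), and accuracy a = TP + TN.
- Rule as written: a·C_correct + (1−a)·C_incorrect, with both averages taken under the current diagnosis.
- Four cells: 30·TP + 36·FN + 12·TN + 15·FP.

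**Step 1: equal accuracy, p = 0.5.** Se 0.9/Sp 0.7 and Se 0.7/Sp 0.9 both have a = 0.80. In 241 patients the first gives 0.05 × 241 ≈ 12 FN and 0.15 × 241 ≈ 36 FP. The second gives about 36 FN and 12 FP. The rule puts the difference at 0. Four cells give:
- Se 0.9/Sp 0.7: 13.5 + 1.8 + 4.2 + 2.25 = 21.75
- Se 0.7/Sp 0.9: 10.5 + 5.4 + 5.4 + 0.75 = 22.05

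The difference is EUR 300 per patient. QALYs behave in the same way. With assumed values TP 1.20, FN 1.10, TN 1.50 and FP 1.45, four cells give 1.3375 and 1.3325, while the rule gives one value for both.

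**Step 2: a better procedure, Se 0.95/Sp 0.85 (a = 0.90), p = 0.5.** Its four-cell cost is 14.25 + 0.90 + 5.10 + 1.125 = 21.375.

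*Current Se 0.9/Sp 0.7:*
- C_correct = (13.5 + 4.2)/0.80 = 22.125
- C_incorrect = (1.8 + 2.25)/0.20 = 20.25
- Current cost = 21.75
- Rule: 0.9 × 22.125 + 0.1 × 20.25 = 21.9375, so **+EUR 188**
- Four cells: 21.375 − 21.75, so **−EUR 375**

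*Current Se 0.8/Sp 0.8:*
- C_correct = (12 + 4.8)/0.80 = 21.0
- C_incorrect = (3.6 + 1.5)/0.20 = 25.5
- Current cost = 21.9
- Rule: 0.9 × 21.0 + 0.1 × 25.5 = 21.45, so **−EUR 450**
- Four cells: 21.375 − 21.9, so **−EUR 525**

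**Step 3: why the first case reverses.** Each error costs more than the matching correct call (36 > 30 and 15 > 12). Yet at Se 0.9/Sp 0.7 the pooled incorrect average is the lower one. AD patients make up 0.45/0.80 = 56% of correct diagnoses but only 0.05/0.20 = 25% of incorrect ones, so the contrast mixes disease status with correctness. At Se 0.8/Sp 0.8 both shares are 50%.

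**Step 4: range.**

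| Current Se/Sp | New Se/Sp | p | Rule (EUR) | Four cells (EUR) |
|---|---|---|---|---|
| 0.9/0.7 | 0.95/0.85 | 0.3 | +92 | −405 |
| 0.9/0.7 | 0.95/0.85 | 0.5 | +188 | −375 |
| 0.9/0.7 | 0.95/0.85 | 0.7 | +105 | −345 |
| 0.8/0.8 | 0.95/0.85 | 0.5 | −450 | −525 |
| 0.7/0.9 | 0.85/0.95 | 0.5 | −1,087 | −525 |
| 0.8/0.8 | 0.9/0.9 | 0.5 | −450 | −450 |

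The rule may reverse the sign, understate a saving, overstate it or be exact. It is exact in the last row because sensitivity equals specificity for both procedures.

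**The case against.** The strongest reply is that this is a condensed article. It does not say in so many words that a single average is used per class, so the sentence could be shorthand for averages within each of the four cells, which goal 1 makes available. The same section describes such models generically: "these models enable the estimation of the likelihood of each consequence and its corresponding costs and effects". That reading is possible. But the specific rule is two-class in both of its sentences, goal 2 pools in the same way, and nothing in goal 3 points to four cells. This is a rule that is stated, not a detail left out.

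Other parts of the reply stand and limit the point.

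- A reader might infer that equally accurate procedures get identical *total* costs. The article does not support that: "A societal viewpoint will be adopted including the evaluation of all relevant costs and effects to calculate the societal benefits". Each test's own cost may therefore enter. Only downstream costs and QALYs are forced equal.
- A reader might infer that the averages must come from the cohort under current diagnosis. The model also draws on literature and expert opinion, so the transfer problem applies to the extent that cohort averages are used.
- A reader might infer that the incremental cost will have the wrong sign. Step 2 shows that this depends on an operating point the article does not give.
- A reader might infer that the drug scenario cannot be right. That scenario belongs to the sensitivity analysis, and the article does not say that the current-practice averages are kept unchanged there.
- True negatives should not be called healthy. They are memory clinic patients who may have another disorder.

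**Conclusion.** The point holds as a defect in a stated rule. Followed as written, the rule makes downstream costs and QALYs a function of overall accuracy alone, and cohort-based averages mix disease status with diagnostic correctness. The algebra needs no assumed values. The size does: in the illustrations the gap between rule and four cells runs from nothing to about EUR 560 per patient (187.5 + 375 = 562.5), and the sign changes in some settings only. All costs, QALY values, prevalences, sensitivities and specificities used here are assumptions.

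Severity is moderate. The Study aim calls this a preliminary economic model for exploring uncertainty. The goal 1 accuracy results, the sample size and the data collection are unaffected, and the model can still be respecified.

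**What to change.** Replace the two sentences in the goal 3 section with a four-cell rule. Each procedure generates proportions of true positives, false negatives, true negatives and false positives, by applying its sensitivity and specificity to the prevalence given by the cohort's reference diagnosis. Costs and utilities specific to each cell are then applied to obtain the procedure's totals. Where a cell is sparse, literature or expert values are used and their uncertainty is carried into the sensitivity analysis.

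This changes model specification only. The classification is already planned under goal 1, and the article already allows outside evidence in the model. The cost is four thinner parameter sets in place of two, and so wider uncertainty. At the assumed Se 0.9/Sp 0.7 and 50% prevalence, for example, the false negative cell would hold only about 12 of 241 patients.

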### Sample size and missing data

A telephone interview is performed for patients who refuse follow-up assessments to determine the reason for refusal, possible cognitive decline and interference with daily activities, and to assess the CDR. Incomplete data will be imputed by means of a regression model. Complete missing data or data missing covariates will be imputed using Rubin’s multiple imputation (MI) procedure.

Sample size is based on an 80% accuracy of current clinical practice to determine correct aetiology [4] and 70% in non-demented patients [49]. Applying a type I error (α = 5%), type II error (β = 80%), drop-out rate of 10% and minimum clinically relevant difference of 10% accuracy increase requires 219 patients to be included in the study.

Contrary to clinical studies, economic evaluations are not based on testing hypotheses. Their goal is to assess decision uncertainty. Therefore, economic evaluations are restricted to the estimation of the uncertainty surrounding cost-effectiveness (expressed in a statistical confidence interval). Within this Bayesian framework, classical inference (and therewith a power analysis) is irrelevant [50].

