### Data assessment

Each centre collects a minimum dataset of clinical information based upon the dataset protocol used for The String of Pearls Initiative – Pearl Neurodegenerative Diseases (http://www.string-of-pearls.org), cost data and data on emerging biomarkers. Table 2 provides an overview of all patient and informal caregiver assessments. Assessments take place at baseline and at 12 and 24 months follow up during a visit (from both patient and informal caregiver) to the memory clinic. Furthermore, several questionnaires were composed in a booklet to measure resource consumption and quality of life. This is filled out by the informal caregiver at baseline, 3, 12 and 24 months.

**Table 2 T2:** Overview of patient and informal caregiver assessments at baseline and follow-up

**Outcome measure**	**Operationalization/type of instrument**	**B**	**T3**	**T12**	**T24**

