#### Quality of life data

Patient’s generic quality of life is measured by the EQ-5D instrument. It was developed and validated in a number of European countries including the Netherlands [30-32] and it has been validated in patients with dementia [33,34]. The EQ-5D describes health status according to five three-level dimensions, which yields 243 potential combinations of health states. Each combination leads to a utility score by means of an additive function derived from the UK general population [35,36].

Patient disease specific quality of life is measured by the validated Quality of Life – Alzheimer’s Disease scale (QoL–AD) [37,38]. It has 13 items covering the domains of physical health, energy, mood, living situation, memory, family, marriage, friends, self as a whole, ability to do chores around the house, ability to do things for fun, money, and life as a whole. Scale scores range from 13 to 52 with higher scores indicating greater QoL. An improvement of 3 points on the QoL-AD is judged as clinically relevant as this indicates a change of well-being on one of the domains from very poor to excellent [39].

Patient EQ-5D is assessed by the patient during the visit to the memory clinic. Furthermore, the informal caregiver judges the EQ-5D and QoL-AD for the situation of the patient and for his/her own situation and fills this out in the booklet of questionnaires.

Care-related quality of life of informal caregivers is assessed by the CarerQol[40]. It combines seven important burden dimensions with a valuation component (a visual analogue scale (VAS)) for happiness. The seven burden dimensions are 1) fulfilment; 2) relational problems; 3) mental problems; 4) problems with daily activities; 5) financial problems; 6) support; and 7) physical problems. The CarerQol-VAS ranges from 0 (“completely unhappy”) to 100 (“completely happy”) and has been validated in a Dutch sample of heterogeneous caregivers.

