#### Cost data

Cost data are retrieved by the composed booklet of questionnaires. Patient resource utilization and caregiver time, which often contains productivity losses, are assessed by means of the short version of the Resource Utilization in Dementia-questionnaire (RUD-lite). This instrument has been validated and proved to register over 95% of the costs involved in AD-care [41]. Work status, income, and productivity losses of both the patient and caregiver are assessed by the adjusted PRODISQ (PROductivity and DISease Questionnaire) [42]. The consequences of informal caregiving on paid or unpaid work are assessed by the Health and Labour Questionnaire on a two-week scale on which is indicated whether one was ill, ill by caregiving or not ill [43]. Additional questions are asked referring to the number of visits to various health care professionals, resources or aids that are bought and other out-of-pocket costs.

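### The telephone fallback for patients who refuse follow-up lists no utility or care-use item, so if the caregiver booklet is also missing, their later costs and utilities rest wholly on imputation

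*Protocol article*

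**What the plan says.** The section Sample size and missing data provides one fallback contact: "A telephone interview is performed for patients who refuse follow-up assessments". Its purpose is "to determine the reason for refusal, possible cognitive decline and interference with daily activities, and to assess the CDR". The next two sentences cover the missing values: "Incomplete data will be imputed by means of a regression model" and "Complete missing data or data missing covariates will be imputed using Rubin’s multiple imputation (MI) procedure".

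The economic data come by a different route. Under Cost data: "Cost data are retrieved by the composed booklet of questionnaires". The booklet also holds the caregiver's EQ-5D and QoL-AD ratings of the patient (Quality of life data). Its schedule, under Data assessment, is: "This is filled out by the informal caregiver at baseline, 3, 12 and 24 months". Clinic visits are fewer: "Assessments take place at baseline and at 12 and 24 months follow up during a visit". Only one utility measure is expressly tied to the visit: "Patient EQ-5D is assessed by the patient during the visit to the memory clinic".

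Research goal 2 uses average costs and consequences of the cohort and of its correctly diagnosed subgroup. Research goal 3 uses average costs and effects of correct and incorrect diagnoses, and derives QALYs by the trapezium rule. The Discussion names the collection of resource use and quality of life as what is unique about the study.

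**The concern.** Apart from the reason for refusal, everything the call collects concerns clinical status. That serves the reference diagnosis (goal 1). It gives goals 2 and 3 no direct observation of where the patient lives, what care is used or how the patient's health state is valued after the refusal.

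This matters if refusal is related to deterioration or to a move into an institution, since costs and utilities after the refusal would then differ from those of attenders. The questions about decline and daily activities suggest that the sponsor considers deterioration possible. Multiple imputation corrects for such a difference only as far as observed variables explain it. Analysis cannot later supply data that were never requested. The booklet already works without a visit at month 3, so a refused visit need not end the collection of economic data.

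**Working it through.** **1. Items listed for the call against items needed.**

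| Needed for goals 2 and 3 | Regular source | In the refuser call? |
|---|---|---|
| Resource use, caregiver time, productivity | Caregiver booklet, months 0, 3, 12, 24 | No |
| Patient EQ-5D, caregiver-rated | Caregiver booklet, same months | No |
| Patient EQ-5D, self-rated | Clinic visit, months 0, 12, 24 | No |
| CDR | Clinic visit, months 0, 12, 24 | Yes |

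Month 3 has a booklet and no visit, so collection without a visit is already part of the design.

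**2. Number of patients.** The only input is the 10% drop-out in the sample-size paragraph. The stated 219 can be reproduced with that rate: 80% against 90% accuracy, two-sided 5%, 80% power (reading the printed type II error of 80% as power) gives 199 by the usual two-proportion formula, and 199 × 1.10 = 218.9. Applied to the enrolled cohort, 0.10 × 241 = 24.1, about 24 patients. This is a ceiling at that rate, because some drop-outs will not be visit refusers and some caregivers may return the booklet anyway. If refusal were 5% to 30% (assumption), the count would be 12 to 72.

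**3. How much of a refuser's QALY would be imputed.** With utilities at 0, 0.25, 1 and 2 years, the trapezium weights are:
- month 0: 0.25/2 = 0.125
- month 3: (0.25 + 0.75)/2 = 0.5
- month 12: (0.75 + 1)/2 = 0.875
- month 24: 1/2 = 0.5

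The sum is 2.0 years. With no booklet from month 12 on, 1.375/2.0 = 69% of the weight is imputed. With only month 24 missing, it is 0.5/2.0 = 25%.

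**4. Size of a possible shift in the cohort mean.** The article gives no figure for refusers' costs or utilities, so the following inputs are assumptions.
- Cost: refusers at k times the attender mean give a true mean of 0.9 + 0.1k (attender mean = 1). If imputation recovers nothing, the estimate is 1.0. For k = 2, 0.1/1.1 = 9.1% too low. For k = 3, 0.2/1.2 = 16.7% too low. If half the excess is recovered, the figures are 0.05/1.1 = 4.5% and 0.1/1.2 = 8.3%.
- Utility: 0.15 lower throughout shifts the mean by 0.10 × 0.15 = 0.015 per year. With months 0 and 3 observed, the loss from month 12 on is 0.10 × 0.15 × 1.375 = 0.021 QALY over two years, or about 0.010 per year.

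**5. Shift in the goal 2 contrast.** Goal 2 compares the whole cohort with the correctly diagnosed subgroup. If refusers form a share d of the cohort and d_c of the subgroup, with the same unrecovered excess (k − 1) times the attender mean, the contrast moves by (d − d_c)(k − 1) times that mean. It is zero when the shares are equal, so a shifted cohort mean is not in itself a biased contrast.

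**The case against.** The case against has four parts, and most of it stands.

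First, a reader might infer that goals 2 and 3 lose the refusers. The article does not support that: the sentences that follow the interview impute both incomplete and completely missing data, so these patients stay in the analysis. Booklets completed before the refusal are also kept, and goal 3 draws on literature and expert opinion as well.

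Second, nothing says that the booklet stops. It is a separate caregiver instrument with its own schedule, and continued collection may already be the practice. On the other hand, the interview is for patients who refuse follow-up assessments, not only visits, and Table 2 lists the booklet items among patient and caregiver assessments. The text leaves both readings open, and a condensed article may leave the detail to the full protocol. The point is therefore conditional on the booklet not being returned.

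Third, a reader might infer that a patient phoned at a month-12 refusal is never called again, and that this call is then taken as the two-year outcome. The article gives no time for the call, schedules the CDR at both month 12 and month 24, and bases the reference diagnosis on the two-year course. That inference rests on silence. The timing of the call is at most a matter for clarification.

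Fourth, the direction of bias is undocumented. Entry requires MMSE of at least 20 and CDR 0 to 1, and patients with only subjective complaints are included, so some refusers may be stable and see no need to return. The phone CDR and the daily-activities item are plausible predictors of cost and would recover part of any difference.

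What remains is the stated content of the call: it contains no economic item, and adding a few would cost little.

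**Conclusion.** The point holds as a cheap improvement, not as a flaw that invalidates goals 2 or 3. The interview is confined to reason for refusal and clinical status. Where the caregiver booklet is also missing, costs and utilities after the refusal depend wholly on imputation, and so on refusers resembling attenders given the observed variables.

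At the planned drop-out at most about 24 of 241 patients are concerned. The 9% and 17% are the largest understatements of mean cost for assumed multipliers of 2 and 3. They require that all drop-outs are refusers without a booklet, that the excess runs over the whole follow-up and that imputation recovers none of it. Neither the size nor the direction of any bias can be established from the article, and the effect on the goal 2 contrast may be smaller than the effect on the mean.

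**What to change.** In Sample size and missing data:

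1. State that refusing the visit does not end booklet collection, and that the caregiver is still asked for the month-12 and month-24 booklets.
2. Where the booklet is also refused, add three items to the call: proxy EQ-5D, place of residence, and hospital or institutional admission since last contact.
3. Use these answers as observed data and, with the phone CDR, as predictors in the multiple imputation.
4. As a clarification only, say when the call is made and whether refusers are contacted at month 24.

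The cost is sending and chasing booklets, plus a few minutes on a call that is already planned. The call becomes slightly longer, and some caregivers will decline, so imputation will still be needed for them.

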### Subjects

For the study, 241 consecutive patients of the participating memory clinics who were suspected of having a primary neurodegenerative disease were included for participating in the study from October 2009 to May 2011; this included all patients with subjective and/or objective memory complaints. Eligibility criteria were chosen to represent the current clinical situation and enable generalisability to clinical practice (see Table 1). Informed consent was obtained from both the patient and the informal caregiver. Gender, age and reason for refusal were obtained for patients unwilling to participate.

**Table 1 T1:** Eligibility criteria for subject selection

*Inclusion criteria*	
-	All new consecutive patients of the participating memory clinics who are suspected of having a primary neurodegenerative disease
-	Mini-Mental State Examination: ≥ 20
-	Clinical Dementia Rating: 0 – 1
-	Availability of a reliable informer or proxy (who visits or contacts the patient at least once a week)
*Exclusion criteria*	
-	Normal Pressure Hydrocephalus, Huntington’s disease
-	Less than two years ago a transient ischaemic attack (TIA) or cerebral vascular accident (CVA) or TIA/CVA followed (within three months) by cognitive impairment
-	Psychiatric history (schizophrenia, bipolar disorder or psychotic problems (not otherwise specified), less than 12 months ago)
-	Major Depression according to the DSM-IV, less than 12 months ago
-	Cognitive problems due to excessive alcohol use (based on clinical judgement)
-	Brain tumour, epilepsy, encephalitis
-	Probably not available for follow-up

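### The sample size names two baseline accuracies, 80% overall and 70% in non-demented patients, but its single figure of 219 is not shown to give 80% power for the 70% case.

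*Protocol article*

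**What the plan says.** The section on sample size and missing data in the protocol article gives two baselines: "Sample size is based on an 80% accuracy of current clinical practice to determine correct aetiology [4] and 70% in non-demented patients [49"]. It adds a 5% type I error and a 10% drop-out rate, and concludes that a "minimum clinically relevant difference of 10% accuracy increase requires 219 patients to be included in the study". It prints "type II error (β = 80" per cent; this is read here as 80% power, because a literal type II error of 0.80 would need only 33 per group.

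The section names no test, sidedness, discordance rate or number of non-demented patients.

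Two other places bear on the point. Under research goal 1, "each index test result for each case is indicated as either true positive, true negative, false positive or false negative", judged against the reference diagnosis, so the clinical and biomarker diagnoses are compared within the same patients. Table 1 admits "Clinical Dementia Rating: 0 – 1" with an MMSE of at least 20, so the cohort may hold both demented and non-demented patients. Enrolment was 241.

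**The concern.** Accuracy of 70% carries more binomial variance than accuracy of 80%, so the same 10-point gain needs more patients from the lower baseline. The lower baseline also applies only to part of the cohort. One total can serve both premises only if it was set by the more demanding one, and 219 looks as if it was not.

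The study's general aim is early diagnosis, and the non-demented patients are the group closest to that aim. A reader of the sample-size paragraph could take a null result in that group as coming from a comparison with 80% power. If the true power were nearer one half, such a result would say little.

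**Working it through.** **Inputs.** From the sample-size paragraph: baselines 80% and 70%, gain 10 points, alpha 5%, power 80%, drop-out 10%, total 219. From the Subjects section: 241 enrolled. Evaluable after 10% loss: 219 × 0.9 = 197 and 241 × 0.9 = 217. Assumed, because not given: sidedness, share of non-demented patients, and phi (the correlation, within patients, between the clinical diagnosis being correct and the biomarker diagnosis being correct).

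**Step 1: reproduce 219.** For two independent proportions with unpooled variance, n per group = (1.960 + 0.842)² × [p1(1−p1) + p2(1−p2)] / 0.10².
- 80% vs 90%: 7.849 × (0.16 + 0.09) / 0.01 = 196.2, so 197; 197/0.9 = 219. With pooled variance n is 199, and 199 × 1.1 = 219.
- One-sided 5%, 75% vs 85% (75% is the midpoint of the two baselines), pooled: 196.8, so 197; 197/0.9 = 219.
- A paired calculation with discordance 0.26 gives 202, and 202/0.9 = 225, which is close to 219.

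The total therefore has more than one possible origin.

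**Step 2: apply the same formulas to 70% vs 80%.**
- Two-sided, unpooled: 7.849 × (0.21 + 0.16) / 0.01 = 290.4, so 291; 291/0.9 = 324. Pooled: 294; 294/0.9 = 327.
- One-sided, pooled: 231; 231/0.9 = 257.
- Two-sided unpaired power at 197 per group is 63%, even if every patient were non-demented.

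**Step 3: the paired design.** The share of patients in whom exactly one diagnosis is correct is psi = p1 + p2 − 2[p1p2 + phi √(p1(1−p1)p2(1−p2))]. McNemar power = Φ{(0.10√n − 1.960√psi) / √(psi − 0.01)}.

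Whole cohort, 80% to 90%:

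| phi | psi | n = 197 | n = 217 |
|---|---|---|---|
| 0 | 0.26 | 79% | 83% |
| 0.5 | 0.14 | 97% | 98% |

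Non-demented patients, 70% to 80%, from 217 evaluable:

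| Assumed share | n | phi 0 (psi 0.38) | phi 0.5 (psi 0.20) |
|---|---|---|---|
| 40% | 87 | 33% | 56% |
| 60% | 130 | 46% | 74% |
| 80% | 174 | 57% | 85% |

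**Step 4: what would be needed.** At a 60% share (n = 130), 80% power requires psi of about 0.17 or less. A 10-point gain already forces psi to be at least 0.10, so the two diagnoses would have to disagree mostly in the biomarker's favour.

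**The case against.** The strongest reply is that the paragraph does not promise a separate test in non-demented patients. It says the size is based on two accuracies and gives one total. Research goal 1 separates aetiology from progression, not demented from non-demented, and speaks of accuracy estimates. If 75% is a blend of the two baselines, the one-sided 75% vs 85% reading uses both premises and gives 219 exactly. This stands in part: the derivation cannot be fixed from the text, and the blended reading is possible. It does not settle the matter, because a total sized for a blended baseline still gives no 80% power at the 70% baseline (257 would be needed), and the reader is not told that a blend was used.

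A reader might also infer that a per-group figure from an unpaired formula, used as a cohort total, leaves the whole study too small. The documents do not support this. Each patient contributes to both sides of the comparison, so one group's worth of patients is roughly what a paired test needs when errors are independent (202 against 197 before drop-out), and positive correlation lowers the need. An unnamed test or discordance rate is also detail that an article may leave to the full protocol, so its absence alone is not a fault.

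Finally, a reader might conclude that 219 definitely fails to deliver 80% power in non-demented patients. That is not proven. With phi 0.5 and an 80% share, 217 evaluable patients give 85%; if all 217 were non-demented, psi up to about 0.28 would still give 80%.

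**Conclusion.** The point holds in a limited form. The article rests its sample size on two accuracies, and none of the readings of 219 examined here is shown to cover the 70% one. By the formulas that reproduce 219 exactly, that case needs 257 (one-sided) or 324 to 327 (two-sided). In the paired design, power for it is below 80% in most of the scenarios examined, but the size of any shortfall rests on the assumed non-demented share (40% to 80%) and assumed phi (0 to 0.5), neither of which the article gives. The whole-cohort comparison of 80% with 90% is adequate and is not in question.

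Severity is moderate: the 219 can be reproduced, enrolment exceeded it, and only the strength of a null result in non-demented patients is affected. Confidence is moderate, because the derivation is inferred.

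**What to change.** Revise the sample-size paragraph in three respects:
- State which premise 219 rests on (80% to 90%, or a blended baseline), with sidedness, and correct the type II error entry so that it reads as power.
- Restate the power for a paired (McNemar) comparison in the whole cohort, with the discordance assumed.
- Present the non-demented comparison as an estimate, with the actual number of such patients and a 95% CI for the paired difference, and not as an 80%-powered test.

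As a guide to the third item, at n = 130 the expected half-width is 1.96 × √((psi − 0.01)/n): 1.96 × √(0.37/130) = 0.105 at phi 0 and 1.96 × √(0.187/130) = 0.074 at phi 0.5 (psi 0.197 before rounding). This is about 7 to 10 points around a 10-point gain.

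The cost is rewording, with no extra patients and no change to the data collected. The stated power becomes less favourable for the non-demented group.
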